### System biological indicators

This omics substudy is exploratory, aiming to identify potential mechanisms of TJC. Blood, urine, and stool samples will be collected from 30 participants per group from Guangdong Provincial Hospital of Traditional Chinese Medicine at baseline (Week 0) and post-treatment (Week 26), including fasting (10 h) blood samples and first-morning mid-stream urine and stool samples. The sample size (*N* = 30/group) is justified for exploratory omics studies (36, 37).
1.Biospecimen collection and processingBlood will be collected into EDTA and serum separation tubes, centrifuged at 3,000 × g for 10 min at 4 °C within 2 h of collection to separate plasma, serum, and peripheral blood mononuclear cells (PBMCs). Urine will be centrifuged at 3,000 × g for 10 min at 4 °C to remove cellular debris, and the supernatant will be aliquoted. Stool will be collected using sterile containers, homogenized, and aliquoted into cryovials. All processing and centrifugation parameters are documented on dedicated log sheets.
2.Cryopreservation and biobankingAll processed biospecimens will be stored in the Guangdong Provincial Hospital of TCM Biobank—a certified biospecimen repository that operates under standardized management systems, has passed CNAS ISO 20387 accreditation for biospecimen quality and competency. The biobank is equipped with dedicated −80 °C freezers fitted with 24/7 temperature monitoring and alarm systems. A complete chain-of-custody log is maintained for each specimen, documenting all handling steps (collection, processing, storage, and transfer) with timestamps and responsible personnel.
3.Outsourced omics analysisAfter sample collection is completed, all biospecimens will be transferred in a single batch to Shanghai Oebiotech Co., Ltd. for professional multi-omics analysis. Shipping will follow validated cold-chain protocols with real-time temperature recording and documented transfer logs. A pre-specified bioinformatics pipeline includes quality control, alignment, differential analysis, pathway enrichment, and multi-omics integration. No external validation is planned; internal QC (technical replicates, pooled QC samples, and coefficient of variation assessment) will ensure data quality.

### Sample size calculation

This is a two-arm, randomized, controlled superiority trial with a placebo control group and a TJC group. Using the composite primary outcome measure and a superiority test for proportions for sample size estimation. Based on literature, the estimated difference between the two groups is 15% (27, 38). With a one-sided *α*=0.025 and power (1-*β*) of 90%, using PASS 15 software for a 1:1 allocation ratio, and accounting for a potential 20% dropout rate (due to loss to follow-up, refusal, exclusion, etc.), a minimum of 265 subjects per group is required, resulting in a total sample size of at least 530 subjects.

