## Introduction

Metabolic Syndrome (MetS) represents a significant global public health challenge in the 21st century (1). It is characterized by a cluster of core components including central obesity, hyperglycemia, hypertension, and dyslipidemia (elevated triglycerides/reduced high-density lipoprotein cholesterol) (2). Its pathophysiological essence involves the superimposition of insulin resistance (IR)-mediated metabolic disorders and a state of chronic low-grade inflammation (3–5). Since its first formal definition by the World Health Organization (WHO) in 1998 (6), the prevalence of MetS has experienced exponential growth, paralleling the global rise in obesity rates and population aging. The latest Chinese epidemiological data (2023 Report on Chronic Diseases and Risk Factors Surveillance in China) indicates that the prevalence of MetS among adults has reached 31.2%, with a notable trend towards younger age groups—the prevalence among individuals under 40 has increased by 47% compared to a decade ago. This population faces not only a high risk of metabolic diseases such as diabetes and non-alcoholic fatty liver disease but also (7–9), due to vascular endothelial injury and accelerated atherosclerosis induced by metabolic disturbances, constitutes a “high-risk group” for cardiovascular and cerebrovascular events (5, 10–12) (e.g., myocardial infarction, stroke). Studies have shown that the risk of cardiovascular events in patients with MetS is 2.3-3.1 times that of healthy individuals, with all-cause mortality increased by 1.8-2.5 times; among these, MetS patients with comorbid diabetes have a 10-year risk of cardiovascular and cerebrovascular events exceeding 40% (13–15). However, current clinical management of MetS predominantly focuses on intervening in individual risk factors (e.g., glucose-lowering, blood pressure control, lipid regulation), lacking multi-target intervention strategies aimed at the “metabolic-vascular injury” network (16). Furthermore, some pharmacological agents (e.g., long-term use of statins, insulin) are associated with side effects such as hepatic and renal impairment and hypoglycemia, making it difficult to meet patients’ needs for “safe, efficient, and holistic regulation” therapeutic approaches. Recent large cardiovascular outcome trials (17, 18) have shown that in high-risk populations with obesity and cardiovascular disease, the annual MACE rate remains substantial despite contemporary standard care.

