Traditional Chinese medicine (TCM) compounds, by virtue of their “multi-component, multi-target, multi-pathway” intervention characteristics, offer novel insights for the comprehensive management of MetS. Meta-analyses have shown that TCM or the combination of TCM and Western medicine can effectively improve metabolic syndrome and reduce cardiovascular and cerebrovascular risk (19–21). Tongmai Jiangtang Capsule (TJC) is an innovative proprietary Chinese medicine developed independently, derived from the classical empirical formula “Method for Boosting Qi, Activating Blood, and Dredging Collaterals.” Its main components include Astragalus membranaceus (Huangqi), Salvia miltiorrhiza (Danshen), Ligusticum chuanxiong (Chuanxiong), Hirudo (Shuizhi), and Pheretima (Dilong), among others. Modern pharmacological studies have confirmed that its core active ingredients (e.g., astragaloside IV, tanshinone IIA, ligustrazine) can ameliorate metabolic disorders through multiple mechanisms (22–26): On one hand, astragaloside IV can activate the AMPK pathway—a key energy sensor that not only enhances insulin sensitivity and inhibits hepatic gluconeogenesis but also exerts anti-inflammatory effects by suppressing NF-*κ*B signaling—thereby ameliorating metabolic disorders; tanshinone IIA can downregulate the expression of inflammatory cytokines (TNF-α, IL-6) in adipose tissue, alleviating IR. On the other hand, ligustrazine and hirudin can inhibit platelet overactivation, reduce hypercoagulability, and simultaneously improve vascular endothelial function and delay the formation of atherosclerotic plaques by modulating the endothelin-1 (ET-1)/nitric oxide (NO) balance. Preliminary studies have indicated that TJC has beneficial effects on both macro- and micro-vascular complications of diabetes, with a good safety profile (27–32); however, its impact on hard cardiovascular and cerebrovascular endpoints (e.g., myocardial infarction, stroke, cardiovascular death) remains unclear.

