### Statistical analysis

A detailed statistical analysis plan (SAP) will be finalized before database lock and unblinding. Statistical analyses will be performed using SAS version 9.4 (SAS Institute Inc., Cary, NC, USA) by the statistics department of the Clinical Research Center at Guangdong Provincial Hospital of Traditional Chinese Medicine. Data from all randomized patients will be analyzed according to the Intent-to-Treat (ITT) principle. Consistent with the CONSORT statement and ITT principle, the last observation carried forward (LOCF) method will be used to handle missing data for the primary analysis.

① Hypothesis Testing: All statistical tests will be two-sided, with a *p*-value less than 0.05 considered statistically significant.② Statistical Description: Normally distributed continuous variables will be described using “mean ± standard deviation,” non-normally distributed continuous variables using “median (interquartile range),” and categorical data using frequencies and percentages.③ Choice of Statistical Methods: Appropriate statistical methods will be selected based on the nature of the data (continuous, categorical, ordinal). Categorical data will be compared using the Chi-square test or Fisher's exact test. For continuous data meeting normality and homogeneity of variance assumptions, the t-test will be used for between-group comparisons; otherwise, the Wilcoxon rank-sum test will be employed. Ordinal data between two groups will be compared using the Mann–Whitney U test, and for multiple groups, the Kruskal–Wallis test. The center effect in the multi-center efficacy evaluation will be analyzed using the Cochran-Mantel-Haenszel method.④ Statistical Analysis Steps: The statistician will follow the pre-specified SAP, meticulously check and confirm the clinical trial data, and then proceed with the statistical analysis. This will include descriptive statistics, baseline comparison of clinical characteristics before treatment, efficacy analysis, safety evaluation, and analysis of excluded and dropped-out cases. If potential confounding factors that are difficult to fully control or were not controlled (e.g., age, disease severity, duration) are imbalanced between groups at baseline, analysis of covariance (ANCOVA) will be used to analyze the impact of these factors on the between-group differences in efficacy, thereby adjusting for the influence of confounders.

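### The stated 90% power for a 15% difference in 3P-MACE is given without event rates and is not supported at the one-year risk that the protocol's own figures suggest

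*Protocol article*

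**What the plan says.** The protocol article's Sample size calculation section sizes the trial on the primary endpoint: "Using the composite primary outcome measure and a superiority test for proportions for sample size estimation". The effect is given in one sentence: "Based on literature, the estimated difference between the two groups is 15% (27, 38"). The other inputs are "With a one-sided *α*=0.025", "power (1-*β*) of 90"%, 1:1 allocation and 20% dropout, with the result that "a minimum of 265 subjects per group is required", or 530 in total. The section gives no event rate for either arm, does not say whether 15% is absolute or relative, and names no superiority margin.

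Three other places bear on it. Study procedure sets 26 weeks of treatment and 26 weeks of follow-up, so events are counted over 52 weeks. The Introduction says that "MetS patients with comorbid diabetes have a 10-year risk of cardiovascular and cerebrovascular events exceeding 40"%. Statistical analysis says "All statistical tests will be two-sided" at 0.05 and that all randomized patients are analysed by intention to treat.

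**The concern.** The sample size for comparing two proportions depends on both event rates, not only on their difference. A 15-point difference can exist only if the control rate exceeds 15%, and under the usual formulas the printed sample size corresponds to a control rate far above that. In a one-year trial of cardiovascular death, non-fatal infarction and non-fatal stroke, this is out of scale with the risk figure that the article itself offers.

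If the real control rate is well below 15%, the trial has little power for any moderate effect. A null result would then say little, and a significant result would tend to overstate the effect. The Abstract and Discussion promise high-level evidence on cardiovascular events, and that promise leans on the 90%.

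**Working it through.** **Inputs.** From Sample size calculation: difference 0.15, one-sided alpha 0.025 (z = 1.960, the same critical value as two-sided 0.05), power 90% (z = 1.282), dropout 20%, 265 per group. From Study procedure: 52 weeks of observation. From the Introduction: more than 40% over 10 years. The control rate is not stated, so it is solved for.

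**1. Reproducing 265.** After 20% dropout, 265 × 0.8 = 212 per arm.

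- Pooled variance: n = [1.960·√(2p̄(1−p̄)) + 1.282·√(p₁(1−p₁) + p₂(1−p₂))]² / 0.15². With p₁ = 0.43, p₂ = 0.28 and p̄ = 0.355, this is (1.326 + 0.857)² / 0.0225 = 211.8, so 212, and 212/0.8 = 265.
- Unpooled variance: n = (1.960 + 1.282)²·[p₁(1−p₁) + p₂(1−p₂)] / 0.15². With 0.443 and 0.293, this is 10.507 × 0.4539 / 0.0225 = 212.0.

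The plan's figure is therefore reproduced at about 43-44% against 28-29%.

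**2. Other readings.**

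- If 265 was reached as 1.2 × 221, the control rate is about 47% (pooled) or 49% (unpooled).
- With a continuity correction it is about 39%.
- Allowing for rounding of N, the lower solutions span roughly 37-50%.
- The formula is symmetric, so there are mirror solutions at 66-72% (about 76% with the continuity correction).
- If 15% is relative, the control rate is about 85% (85% against 72.25% gives 270 per group).

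**3. One-year risk on the protocol's scale.** At constant hazard, the one-year risk is 1 − (1 − R)^(1/10).

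- R = 40%: 1 − 0.6^0.1 = 4.98%. The back-solved 43-44% is about nine times this.
- R = 80% (assumed): 1 − 0.2^0.1 = 14.9%.
- Conversely, 44% in one year would mean 1 − 0.56^10 = 99.7% over 10 years.

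At 5% the largest possible absolute reduction is 5 points. At 15%, a 15-point reduction would mean removing every event.

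**4. What 530 patients give.** Exact power of the pooled z-test, two-sided 0.05. The control rates are assumptions. Columns are for 212 per arm (after dropout) and 265 per arm (all randomized).

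| Control rate, 52 weeks | Power for 30% relative reduction: 212 | 265 | Relative reduction detectable with 90% power: 212 | 265 |
|---|---|---|---|---|
| 5% | 12% | 13% | 92% | 86% |
| 10% | 19% | 24% | 74% | 68% |
| 15% | 28% | 35% | 62% | 57% |
| 20% | 38% | 45% | 55% | 50% |

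**The case against.** **No printed number is wrong.** The formula does return 265, and an article may leave arm rates to the full protocol. Both are fair. The absence of the rates is not the point by itself; the point is that the article prints a power claim that does not fit its own risk scale.

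**The control rate is inferred.** A reader might conclude that the sponsor assumed 44%, or that 66-72% is the only alternative. The document supports neither. It mentions a superiority test without a margin. If a margin had been used (an assumption), 212 per arm would solve, with unpooled variance, at about 26% against 11% (3-point margin), 20% against 5% (5-point) or 17% against 2% (6-point). All of these still need a control rate above 15%. They also need relative reductions of 15/26 = 58%, 15/20 = 75% and 15/17 = 88%.

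**The 10-year figure is a lower bound for another group.** It concerns MetS with diabetes. The trial enrols patients aged 65 or over with established disease or another high-risk criterion, and excludes acute events only within the past 14 days. Its endpoint also takes in silent infarction, imaging-positive TIA and micro-bleeds. The true rate may therefore exceed 5%. However, the article itself doubts whether the last two items belong in the primary endpoint, and the visit schedule lists no brain MRI.

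**The denominator.** Intention-to-treat analysis uses 265 per arm, which helps: a halving from a 20% control rate then has 90.5% power. That stands, and is why both denominators are shown.

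**A true 15-point difference from a lower control rate would be easier to detect.** This is correct: 20% against 5% has over 99% power with 212 per arm. The difficulty is the assumed difference itself, not the control rate alone.

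**Conclusion.** The concern holds as one of scale. On the protocol's own 10-year figure, a 15-point absolute reduction in 52 weeks is out of reach, and the stated 90% power is not supported. At control rates of 5-20%, 90% power exists only for relative reductions of about 55-92% (212 per arm) or 50-86% (265 per arm).

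This rests on reading 15% as absolute, on a test without a margin for the back-solved rates, on constant hazard for the annual rate, and on assumed control rates for the power table. The one-sided and two-sided wordings share the same critical value and change nothing.

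Two stronger readings are not supported. One is that the protocol strictly contradicts itself: the 10-year figure is open-ended and describes a different population, so it does not exclude a higher rate. The other is that reference 27 cannot support the effect. The Introduction groups it with preliminary studies and says of the capsule that "its impact on hard cardiovascular and cerebrovascular endpoints (e.g., myocardial infarction, stroke, cardiovascular death) remains unclear", but neither that source nor reference 38 is available here, so what event data they hold cannot be judged.

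**What to change.** In Sample size calculation, state the assumed 52-week 3P-MACE rate in each arm with its source, whether 15% is absolute or relative, and any superiority margin. Replace the 90% figure with the power and detectable effect that 530 patients give over a plausible range of control rates, naming the denominator used.

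State that 3P-MACE will be reported as an estimate with a confidence interval and that a non-significant result does not show absence of effect. Temper the claims of high-level evidence in the Abstract, Introduction and Discussion to match.

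The cost is rewording and a much less favourable power statement. No added enrolment is needed, and treatment and visits are unchanged.

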### Randomization

Subjects who sign the informed consent form and meet the study criteria will be assigned a unique drug code via a central randomization system. Eligible subjects will be enrolled into groups sequentially according to time order and drug code. A computerized randomization schedule will be generated using the PROC PLAN procedure in SAS software. Study drugs will be coded according to the randomization schedule and then allocated to subjects. Note: Patients who fail screening but are suitable for re-screening must retain their original screening number. Drug codes for patients who are successfully screened and randomized but do not receive treatment cannot be reassigned to others. The next successfully screened patient will be assigned the next sequential drug code.

### Blindness

A double-blind design will be implemented. All investigators, subjects, physicians, drug administrators, and dispensing nurses will remain blinded to the treatment assignment until the study is completed and the database is locked. The blinding procedure will be managed by the clinical research unit leader, sponsor, and statistician. Unblinding will only be permitted in the event of a serious adverse event where knowledge of the treatment assignment is necessary for clinical management. The patient's group assignment will be obtained from the drug administrator.

Both TJC and its matching placebo are manufactured by Baoding Buchang Tianhao Pharmaceutical Co., Ltd. The main components of the TJC placebo are starch, bitter acid, and dextrin. It is identical to the active drug in appearance, size, color, dosage form, weight, taste, and odor. Furthermore, the quantity stated on the investigational product packaging will be blinded. The standard label for the investigational product will include the drug code, name of the clinical investigational product, indication, dosage and administration, treatment course, storage conditions, batch number, expiration date, and the supplier of the investigational product.

### Data collection and management

Investigators will enter raw data into the electronic CRF (eCRF) accurately and promptly based on the original observations from the subjects, strictly adhering to the trial protocol. To ensure data accuracy, two dedicated data entry personnel will perform independent double data entry and verification. Monitors will verify that all eCRFs are complete and consistent with the source data, querying any discrepancies as they arise. Researchers must promptly correct any errors or omissions identified.

### Monitoring

To further ensure clinical trial quality, the fundamental principles of “Quality by Design” and process control will be followed. Before the study begins, the sponsor will train all investigators and study coordinators at all centers to ensure consistency in drug administration and procedures. The sponsor will appoint monitors to conduct systematic monitoring of the trial in accordance with the principles of Good Clinical Practice (GCP), ensuring that the protocol is adhered to and that the data recorded in the CRFs are consistent with the source data.

### Statistical analysis

A detailed statistical analysis plan (SAP) will be finalized before database lock and unblinding. Statistical analyses will be performed using SAS version 9.4 (SAS Institute Inc., Cary, NC, USA) by the statistics department of the Clinical Research Center at Guangdong Provincial Hospital of Traditional Chinese Medicine. Data from all randomized patients will be analyzed according to the Intent-to-Treat (ITT) principle. Consistent with the CONSORT statement and ITT principle, the last observation carried forward (LOCF) method will be used to handle missing data for the primary analysis.

① Hypothesis Testing: All statistical tests will be two-sided, with a *p*-value less than 0.05 considered statistically significant.② Statistical Description: Normally distributed continuous variables will be described using “mean ± standard deviation,” non-normally distributed continuous variables using “median (interquartile range),” and categorical data using frequencies and percentages.③ Choice of Statistical Methods: Appropriate statistical methods will be selected based on the nature of the data (continuous, categorical, ordinal). Categorical data will be compared using the Chi-square test or Fisher's exact test. For continuous data meeting normality and homogeneity of variance assumptions, the t-test will be used for between-group comparisons; otherwise, the Wilcoxon rank-sum test will be employed. Ordinal data between two groups will be compared using the Mann–Whitney U test, and for multiple groups, the Kruskal–Wallis test. The center effect in the multi-center efficacy evaluation will be analyzed using the Cochran-Mantel-Haenszel method.④ Statistical Analysis Steps: The statistician will follow the pre-specified SAP, meticulously check and confirm the clinical trial data, and then proceed with the statistical analysis. This will include descriptive statistics, baseline comparison of clinical characteristics before treatment, efficacy analysis, safety evaluation, and analysis of excluded and dropped-out cases. If potential confounding factors that are difficult to fully control or were not controlled (e.g., age, disease severity, duration) are imbalanced between groups at baseline, analysis of covariance (ANCOVA) will be used to analyze the impact of these factors on the between-group differences in efficacy, thereby adjusting for the influence of confounders.

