**Methods:**

This is a randomized, double-blind, placebo-controlled, multicenter trial. A total of 530 participants aged ≥65 years, diagnosed with MetS and the TCM pattern of Qi Deficiency and Blood Stasis, and at high CCV risk, will be enrolled. They will be randomly assigned (1:1) to receive either TJC or a matched placebo, in addition to standard care, for 26 weeks, followed by a 26-week follow-up. The primary endpoint is the composite of 3P-MACE (cardiovascular death, non-fatal myocardial infarction, non-fatal stroke). Secondary endpoints include metabolic parameters, vascular assessments, TCM symptom scores, and quality of life. Omics analyses will explore potential mechanisms. The trial was registered on ClinicalTrials.gov (NCT06908473).

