### Study procedure

The schedule of study procedures is outlined in Table 1. The study will include a screening/baseline period, a treatment period, and a follow-up period. The screening/baseline period will last 2 weeks, the treatment period will be 26 weeks, and the follow-up period will be 26 weeks. Patients will be required to provide written informed consent after a complete explanation of the study during the screening period.

**Table 1 T1:** Study schedule.

Research phase	Screening/baseline	Treatment phase			Observation phase after intervention
Number of visits	Visit 1	Visit 2	Visit 3	Visit 4	Visit 5
Visit time point	D-7–0	Week 4 ± 4 days	Week 12 ± 4 days	Week 26 ± 4 days	Week 52 ± 4 days

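### LOCF for the primary analysis records participants who leave without a 3P-MACE event as event-free for follow-up that was never observed, and the ITT principle does not justify this

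*Protocol article*

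**What the plan says.** The abstract defines the endpoint: "The primary endpoint is the composite of 3P-MACE (cardiovascular death, non-fatal myocardial infarction, non-fatal stroke". Under Study procedure, "the treatment period will be 26 weeks, and the follow-up period will be 26 weeks", and Table 1 marks the composite outcome at every visit through Visit 5 at week 52.

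The Statistical analysis section sets the population: "Data from all randomized patients will be analyzed according to the Intent-to-Treat (ITT) principle". It then fixes the missing-data rule: "the last observation carried forward (LOCF) method will be used to handle missing data for the primary analysis", introduced as consistent with CONSORT and ITT. On tests, it says that "Categorical data will be compared using the Chi-square test or Fisher's exact test", with a Cochran-Mantel-Haenszel analysis for centre.

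The Sample size calculation treats the endpoint as a proportion: "Using the composite primary outcome measure and a superiority test for proportions for sample size estimation". It arrives at 265 per group after "accounting for a potential 20% dropout rate (due to loss to follow-up, refusal, exclusion, etc".). The article describes no censoring rule and no time-to-event method.

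**The concern.** 3P-MACE accrues over time. If someone leaves at week 12 with no event, the value carried forward is no event, and that person enters the week-52 count as though followed and found event-free. A participant with an infarction or stroke recorded before leaving keeps it, so only those who leave event-free are affected.

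There are two consequences. Counted event rates are too low in both arms, which shrinks the absolute difference even when dropout is balanced. If dropout is unbalanced, the arm that loses more people, or loses them earlier, looks better protected. The filled-in values are also treated as observed, so the standard error does not reflect what is unknown.

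The schedule makes this more than theoretical. After week 26 the only scheduled visit is week 52, so someone lost after week 26 can have up to half of the follow-up filled in. The stated justification is also wrong: ITT concerns who is analysed and in which arm, not what is assumed about outcomes that were not observed.

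**Working it through.** **Inputs from the article.** 265 per group, 1:1; 20% dropout allowance, at most 0.20 × 530 = 106 people; difference of 15 points; power 90%; one-sided 0.025 for sizing and two-sided 0.05 for analysis (the same critical value, 1.96).

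**Inputs assumed.** Event rates and the split of dropout by arm, because the article gives neither.

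**The plan's own figure.** 265 cannot be checked uniquely, because no arm event rate is stated. The pooled two-proportion formula gives 212 evaluable per arm at 43% versus 28%, and 212 / 0.8 = 265. The mirror pair, 72% versus 57%, gives the same. Lower rates need fewer: 20% versus 5% needs 101, or 127 after dropout. The LOCF point does not depend on this figure, but it shows that the sizing corresponds to high event rates. I therefore use a range of 5% to 40%.

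**Model.** Constant, independent hazards over 52 weeks. With true 52-week risk p and dropout d:

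- h = −ln(1 − p), l = −ln(1 − d)
- proportion counted under LOCF: q = h/(h + l) × [1 − (1 − p)(1 − d)]

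Rough check: if people leave halfway on average, q ≈ p(1 − d/2), which is 0.90p at d = 20%.

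**1. Equal dropout of 20%, true 40% versus 25%.**

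- Control: h = 0.5108, l = 0.2231; q = 0.6960 × (1 − 0.60 × 0.80) = 0.6960 × 0.52 = 0.3619
- TJC: h = 0.2877, l = 0.2231; q = 0.5632 × (1 − 0.75 × 0.80) = 0.5632 × 0.40 = 0.2253
- Difference: 0.3619 − 0.2253 = 0.1366, or 13.7 points instead of 15
- Risk ratio: 0.622 against a true 0.625, essentially unchanged

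True rates of 5, 10, 20 and 40% are counted as 4.5, 9.0, 18.0 and 36.2%.

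**2. No true effect, unequal dropout.** Worked case: p = 0.40, dropout 15% on control and 25% on TJC.

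- Control: 0.5108/0.6733 × (1 − 0.60 × 0.85) = 0.7586 × 0.49 = 0.3717
- TJC: 0.5108/0.7985 × (1 − 0.60 × 0.75) = 0.6397 × 0.55 = 0.3518
- False difference: 0.0199
- SE at 265 per arm: √[(0.3717 × 0.6283 + 0.3518 × 0.6482)/265] = 0.0417; shift = 0.0199/0.0417 ≈ 0.48
- Two-sided rejection: Φ(0.48 − 1.96) + Φ(−0.48 − 1.96) ≈ 0.076

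| True rate, both arms | False difference, 15% vs 25% | Rejection | False difference, 10% vs 30% | Rejection |
|---|---|---|---|---|
| 5% | 0.3 points | 5.3% | 0.5 points | 6.0% |
| 10% | 0.5 | 5.5% | 1.1 | 7.1% |
| 20% | 1.0 | 6.1% | 2.1 | 9.6% |
| 40% | 2.0 | 7.6% | 4.0 | 15.9% |

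Equal dropout under no effect leaves rejection at 5%.

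**3. Bias in the other direction.** True 40% versus 25%, dropout 25% on control and 15% on TJC: counted rates are 0.3518 and 0.2316, a difference of 12.0 points. Power is about 86%, against 96% with complete follow-up of 265 per arm. Part of that loss would occur under any method, because follow-up is missing.

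**The case against.** The article defers detail to a SAP, so one could say that the primary analysis is not yet settled. That does not remove the point: the LOCF sentence is a positive commitment, and a SAP would have to reverse it. The planned analysis of excluded and dropped-out cases does not change the primary rule either.

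Other objections do limit the point:

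- The dropout splits are assumed. The trial is double-blind with a matched placebo, and the Discussion describes mainly mild gastrointestinal reactions, so a large imbalance is not established. At 5% to 10% event rates the 15% versus 25% split gives only 0.3 to 0.5 points.
- 106 is an upper bound on unknown event status, since the allowance also covers refusal and exclusion.
- The chi-square test is not assigned by name to 3P-MACE, and week 52 is not named as the primary time point. Both are inferred from the sizing method, the rule for categorical data and Table 1.

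A reader might also infer stronger claims that the documents do not support:

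- That every dropout is counted as event-free. Events recorded before leaving are kept.
- That non-cardiovascular deaths are miscounted. Someone who dies of a non-vascular cause without a prior 3P-MACE event truly has none.
- That LOCF causes dilution of an on-drug effect over the 26 weeks off drug. That comes from the design, and a 52-week hazard ratio would average over the same two periods.
- That LOCF is prescribed for the repeated continuous outcomes. The sentence covers only the primary analysis.

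**Conclusion.** The concern holds in this form: the article fixes a missing-data rule for the primary analysis that assumes no event in unobserved time, and wrongly derives it from ITT. Balanced 20% dropout understates event rates by about 10% in relative terms and takes a 15-point difference to about 13.7, with the risk ratio almost intact. Unbalanced dropout biases the comparison: at an assumed 15% versus 25%, by about 0.3 to 2.0 points, with type I error of about 5.3% to 7.6%, across event rates of 5% to 40%.

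These sizes rest on constant hazards, dropout independent of outcome, and event rates and splits that the article does not give. The bias is modest at low event rates. It could be larger if people leave because their health is worsening, which this model leaves out. The direction cannot be known in advance, since it depends on which arm loses more follow-up.

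**What to change.** Delete LOCF and its ITT/CONSORT justification for the primary outcome. In its place, specify:

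- Time from randomisation to first 3P-MACE adjudicated by the Clinical Events Committee, through week 52, in all randomised participants, censored at the last date on which event status is known.
- A centre-stratified log-rank test and Cox hazard ratio, with cumulative incidence treating non-cardiovascular death as a competing event.
- A sensitivity analysis for informative dropout, such as a tipping-point analysis, because censoring also assumes that those who leave resemble those who stay.

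Under the independent-dropout assumption used above, censoring removes the bias shown in the table.

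The cost is small: event dates and last-contact dates must be captured, and programming is slightly heavier. The committee already adjudicates all suspected endpoints, and the article says the SAP will be finalised before database lock and unblinding, so the change can be made in time.
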